#### Secondary analyses

An identical logit model will be used for ICU mortality after urgent ICU admission where the PICU admission was initiated in a hospital ward, ICU mortality after urgent ICU admission initiated in the OR, unplanned hospital re-admission within 2 days of hospital discharge and mortality following DNR orders.

Significant clinical deterioration events, Code Blue events, stat calls and urgent PICU consultations per 1000 patient-days will be evaluated using Poisson regression using hospital-level aggregated count data. The independent variables will include a dummy indicator for treatment arm, the baseline event rate and hospital size stratification variable. A linear regression model, in which the within-hospital mean is the dependent variable, will be used to evaluate the nature of SCDE, inpatient ward patient-days, and for patients admitted urgently to the PICU, PIM2 score, PELOD score, ventilator-free days, ICU patient-days and ICU therapy-days. The independent variables will include a dummy indicator for treatment arm, the baseline means and hospital size stratification variable. The analysis will be weighted by the size of the hospital.

An identical linear regression model will be used to evaluate the frequency of vital sign documentation from the randomly selected patient records. Since the number of records abstracted will be the same in each hospital, weighting will not be necessary. Documentation will be evaluated as follows: the number of heart rate, respiratory rate, systolic blood pressure, trans-cutaneous oxygen saturation, capillary refill, oxygen therapy and respiratory effort measurements, and the number of times that all seven items were documented will be compared for patients in hospitals with and without BedsidePEWS. All analyses will adjust for baseline event rates and hospital strata. Linear regression will be used to compare the numbers of (1) vital signs documented, (2) documented physician visits, (3) the nurse: patient ratio, the use of (4) continuous ECG monitoring and (5) continuous pulse oximeter monitoring with the BedsidePEWS scores calculated from the abstracted clinical data.

Analysis of the documentation and interaction survey and the post-study decision-maker survey data will compare groups using linear regression weighted by the size of the hospital.

The following four pre-specified subgroup analyses will be performed. (1) Hospital size. Hospitals will be classified on the basis of the number of eligible inpatient ward beds. Hospitals with ≥200 eligible inpatient ward beds will constitute one group and those with <200 eligible inpatient ward beds the other. This is consistent with the stratification method used for randomization. (2) Hospitals with and without MET-RRT. (3) Hospitals with ECMO for children. (4) Patients with urgent PICU admission initiated in an inpatient ward.

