### Secondary outcomes: process of care

The study includes five processes of care assessments: (1) ‘Stat’ calls. This was formally defined (Table 3), and a consistent approach to data collection was applied throughout the study, recognizing that cultural and other factors may contribute to considerable inter-hospital variability. (2) Code Blue calls for immediate medical assistance of the resuscitation team and equipment. (3) Urgent consultations (within 15 min) to the ICU or MET-RRT. (4) Using documentation from five randomly (central computerized randomization) selected patients each week, physician visits, the nurse:patient ratio and the use of continuous monitoring are described. (5) Frontline staff complete the documentation and interaction survey (2 pages, <10 min to complete) that describes their perceptions of the documentation system and the nature of interactions with physicians (Additional file 2: CRF). This custom-built survey was developed and used in our pilot evaluations of BedsidePEWS. It has not been formally validated.

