### Sample size and assumptions

Power calculations are based on population estimates derived from 14 local hospitals’ data using a published method for cluster RCTs [61]. For all-cause mortality we found a baseline rate of 5.1/1000. The steering committee agreed that a mortality reduction of less than 1/1000 admissions would not be a compelling reason to modify practice. A study with 20 hospitals can show an 18% relative risk reduction in mortality (absolute risk reduction 0.09%), given alpha = 0.05 (2-sided), power = 80%, mean of 119 pediatric beds, length of stay = 4 days, with 0.90 average occupancy, k = 0.15, *n* = 20, baseline rate = 5.1/1000. The quantity k is the coefficient of variation for mortality between hospitals. Assuming attrition of 1-2 hospitals, we will include a sample of 22 hospitals.

Data from 4 pediatric hospitals in Ontario indicate there are 1052 urgent ICU admissions/year, of which we estimate 40% involve SCDE, for a rate of 2 per thousand patient days. Thus, with 20 sites we will be able to show a 31% reduction in SCDE [alpha = 0.05 (2-sided), power = 80%, k = 0.15, where k is the coefficient of variation for SCDE rate between hospitals]. The value of k allows for a moderate amount of clustering within hospital.

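### Poisson regression on hospital counts leaves out the extra-Poisson variation that the sample size assumes, so type I error for the main secondary outcome (SCDE) is about 2 to 5 times nominal

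*Protocol article*

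**What the plan says.** The Secondary analyses section groups four outcomes, each expressed per 1000 patient-days: SCDE, Code Blue events, stat calls and urgent PICU consultations. They "will be evaluated using Poisson regression using hospital-level aggregated count data". The covariate list follows: "The independent variables will include a dummy indicator for treatment arm, the baseline event rate and hospital size stratification variable". No dispersion scale, hospital random effect, robust variance or reference distribution is mentioned.

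The Sample size and assumptions section plans SCDE differently. It takes 40% of urgent ICU admissions as SCDE, "for a rate of 2 per thousand patient days", and derives a detectable 31% reduction with 20 sites using "k = 0.15, where k is the coefficient of variation for SCDE rate between hospitals". It adds: "The value of k allows for a moderate amount of clustering within hospital". For stat calls, the process-of-care section accepts that "cultural and other factors may contribute to considerable inter-hospital variability".

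The other models in the Data analysis section regress a hospital-level logit or mean on the same kind of covariates. Their residual variance is estimated from the scatter between hospitals.

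**The concern.** With one count per hospital, a Poisson model fixes the variance of that count at its mean. If true rates differ between hospitals by more than the covariates explain, the counts scatter more widely than this. The model has no term to register the excess, so the standard error of the arm effect is too small and the test rejects too often.

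The sample size calculation says that such variation exists, so planning and analysis rest on different variance assumptions. SCDE is the main secondary outcome, and the article concedes under Limitations that mortality may be too rare to show important differences. A nominally significant SCDE result could then carry much of the interpretation.

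**Working it through.** **Inputs from the protocol article.** SCDE rate 2 per 1000 patient-days; k = 0.15; two-sided alpha 0.05; power 80%; 20 hospitals (10 per arm), 22 recruited; 119 beds at 0.90 occupancy with 4-day stay (given in the mortality sentence); 26 weeks of baseline and 52 of follow-up; Discussion forecasts of 400,000 patient-days, 1900 urgent ICU admissions and 200 cardiac arrests.

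**Step 1: the plan's own 31%.** The usual unmatched cluster formula for rates is c = 1 + (1.96 + 0.84)² × [(λ0 + λ1)/y + k²(λ0² + λ1²)] / (λ0 − λ1)², with c hospitals per arm and y patient-days per hospital.
- At y = 119 × 0.90 × 365 = 39,092, the detectable reduction is 22.6% (21.6% without the added 1), not 31%.
- About 31% appears at a smaller volume: 30.7% at y = 9,773 without the added 1, and 30.1% at y = 12,121 with it.
- The SCDE sentence gives no patient-days, so the article does not settle which volume was used. I therefore carry all of them forward.

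**Step 2: expected SCDE per hospital in 52 weeks (m).**
- 31% volume: 9,773 × 0.002 = 19.5.
- Discussion: 400,000/22 = 18,182 patient-days, giving 36.4. If that total covers all 78 weeks, 18,182 × 52/78 = 12,121, giving 24.2. As a cross-check, 1900 × 0.40 / 22 = 35.
- Planning volume: 39,092 × 0.002 = 78.2.

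**Step 3: dispersion and true error.** Without baseline adjustment, φ = 1 + m k². With adjustment, and hospital rates perfectly stable over time (the most favourable case), φ = 1 + m k²(1 − R). Here R = k²/(k² + 1/b) is the reliability of the baseline rate and b = m/2 its event count. True type I error is 2[1 − Φ(1.96/√φ)].

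Example at planning volume: 1 + 78.2 × 0.0225 = 2.76, error 23.8%. With b = 39.1, R = 0.0225/(0.0225 + 0.0256) = 0.47, so φ = 1 + 1.76 × 0.53 = 1.94, error 15.9%.

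The last column is a null simulation of the planned model with arm, baseline rate, stratum and a patient-days offset (22 equal-sized hospitals, 4,000 runs). The correlation of true log rates between baseline and follow-up was set at 1, 0.7 and 0.

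| Volume | m | φ unadjusted | Error | φ adjusted, stable rates | Error | Simulated, planned model |
|---|---|---|---|---|---|---|
| Where 31% reproduces | 19.5 | 1.44 | 10.2% | 1.36 | 9.3% | 9.3–10.3% |
| Discussion, 78-week reading | 24.2 | 1.55 | 11.5% | 1.43 | 10.1% | 10.4–11.7% |
| Discussion, 52-week reading | 36.4 | 1.82 | 14.6% | 1.58 | 11.9% | 11.5–14.8% |
| 119-bed planning | 78.2 | 2.76 | 23.8% | 1.94 | 15.9% | 16.3–25.2% |

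Further runs with 20 hospitals reached 16% at about 35 events. Unequal hospital sizes, an assumption because the article gives no spread, raised the error to about 17% at the Discussion volume and about 30% at the planning volume. With k = 0 the Poisson test held about 5%, which isolates the cause.

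**Step 4: the other three outcomes.**
- Code Blue: no rate is given. Using cardiac arrests as a rough guide, 200/22 = 9.1 per hospital, or 6.1 on the 78-week reading. At k = 0.15, φ = 1.14–1.20 and the unadjusted error is 6.6–7.4%; simulation gave 6–8%. At an assumed 0.5 per 1000 and planning volume it would be 9–11%.
- Consultations: no rate or k is given. At planning volume and an assumed k of 0.15, a rate of 2 per 1000 would match SCDE (16–25%), and 5 per 1000 would give 20–45%.
- Stat calls: no rate or k is given either. The error rises with m k².

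**Step 5: the same model with a Pearson scale and t reference.** Simulated type I error for SCDE was 4.4–5.9% with equal-sized hospitals and about 5.3–7.5% with unequal sizes (assumed size CV 0.6).

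**The case against.** The strongest reply is that the article gives the model family, aggregation level and covariates, and leaves the variance estimator to an analysis plan that is not shown. The same text does not state a patient-days offset, which everyone would assume. It is true that an unseen plan may add a dispersion term. But the article goes beyond naming a family: it lists covariates and says where weighting is and is not needed. Taken at face value, Poisson regression means variance equal to the mean, which conflicts with the stated k.

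A second reply is that baseline adjustment deals with hospital differences. It does so in part: at planning volume the error falls from 24% to 16% if rates are perfectly stable. A reader might infer that the model ignores between-hospital variation, and that goes too far. Nor does adjustment cure the problem, because the baseline has half the exposure. Even with stable rates, φ tends to 1 + m/b = 3 as m k² grows, an error of about 26%.

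A reader might also infer a three- to five-fold inflation or worse for all four outcomes. The article does not support that. The range holds for SCDE only at the 119-bed volume, Code Blue is near nominal at arrest volumes, and any large figure for stat calls needs a rate and k that must be invented. The primary mortality analysis does not share the defect.

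**Conclusion.** The concern holds in a bounded form. As written, the count model understates the standard error of the arm effect whenever the between-hospital variation assumed in the sample size section is present. For SCDE the true type I error is about 9–16% at 20–36 events per hospital and about 16–25% at about 78 events, roughly 2 to 5 times nominal.

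This rests on k = 0.15, a rate of 2 per 1000 patient-days, 20–22 hospitals of equal size, and a baseline-to-follow-up correlation between 0 and 1. Which end of the range applies depends on which of the article's volumes is right. Code Blue inflation is small (about 6–8%) under the cardiac-arrest proxy and k = 0.15. For consultations and stat calls only the direction is established: the more frequent and variable the calls, the larger the inflation.

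**What to change.** In Secondary analyses, replace Poisson regression for the four count outcomes with quasi-Poisson regression. Estimate the scale from the Pearson statistic and use a t reference on the residual hospital degrees of freedom: 20 hospitals less 4 coefficients (intercept, arm, baseline rate, stratum) leaves 16. A negative binomial model, or a Poisson model with a hospital random effect, would also serve if a small-sample correction is named. Keep the same covariates and state the log patient-days offset. If the full analysis plan already does this, citing it in the same sentence is enough.

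The cost is one sentence and no new data. Standard errors for SCDE grow by √φ, from √1.36 = 1.17 to √2.76 = 1.66 times the Poisson value across the table above, and the t quantile adds a little. This is the correct width, and because the 31% figure was computed with k = 0.15, the planned power already allows for that variation. The change should be recorded before the final data set is analysed.

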### Intervention: BedsidePEWS

The BedsidePEWS documentation-based system of care replaces existing documentation systems for vital signs in inpatient ward areas in hospitals randomized to the intervention. There are four elements in the system: (1) the BedsidePEWS score; (2) the BedsidePEWS documentation record; (3) score-matched care recommendations, developed using the responses of 280 healthcare professionals (80 community, 200 referral) surveyed to determine ‘reasonable’ care in each of the domains of vital sign assessment, secondary review, continuous monitoring and ICU consultation, and customized for each implementation; (4) the education program, developed by two nurse educators to support implementation and maintain expertise, including the BedsidePEWS Instructor course and frontline education program.

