### Secondary outcomes: clinical

The main secondary outcome is the significant clinical deterioration event (SCDE), a composite outcome comprised of the treatment(s) provided or death prior to transfer from an inpatient ward. An SCDE is defined as the provision of significant pre-specified respiratory or circulatory therapies or cardiopulmonary resuscitation in the 12 h before transfer from the inpatient ward or during the hour after transfer, or death without a DNR order in an inpatient ward (Table 2).

EPOCH includes eight additional clinical outcomes (Table 3): (1) the nature of SCDE rated on the seven-point Children’s Resuscitation Intensity Scale (Table 4), which measures the timing of interventions in children for whom active resuscitation is anticipated; (2) potentially preventable cardiac arrest in patients experiencing a cardiac arrest while in an eligible inpatient ward. This excludes patients with a preceding DNR order. Potentially preventable is defined as the degree to which ‘events may have been avoided given the application of reasonable current (2011-13) standards of practice by an average practitioner and system anticipated to manage the condition in question’ [53-57]. Events with a consensus rating from two expert reviewers of ≥4/6 are defined as potentially preventable cardiac arrests (Table 5) [55,56]. (3) Unplanned hospital re-admission; (4) urgent PICU re-admission, both within 48 h of discharge. Finally, in all patients admitted urgently to the PICU from a hospital inpatient ward measurement was made of: (5) the predicted risk of mortality (PIM2 score) [58,59], (6) PICU mortality, (7) organ dysfunction (PELOD score) [60] and (8) ventilator-free days to 28 days. Urgent PICU admission is defined as departure from the inpatient ward within 6 h of the decision to admit to the ICU (Table 2). This definition reflects the need to pragmatically distinguish between urgent and elective admission and the recognition that most urgent admission occurs within 1-2 h of the decision to transfer to an ICU.

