**Table 3 Tab3:** **EPOCH secondary outcomes**

**Clinical**	
(1) Significant clinical deterioration event	See Table 4
(2) The nature of clinical deterioration events	Clinical deterioration events will be described by using the Children’s Resuscitation Intensity Scale (Table 4). Urgent PICU admissions that are initiated when the patient is in the operating room will not be regarded as clinical deterioration events
(3) Potentially preventable cardiac arrest	Assessment of the potential preventability of cardiac arrest will be determined for all patients who had a cardiac arrest event while in an eligible inpatient ward, without a preceding DNR order (Table 5)
	Thus, potential preventability ratings of 4: ‘more than likely (more than 50/50, but “close call”);’ 5: ‘strong evidence of preventability;’ 6: ‘virtually certain evidence of preventability’ will be deemed potentially preventable cardiac arrest events
	Preventability will be rated by blinded reviewers reviewing anonymized and delinked clinical data presented in a standardized format. If consensus between the two initial reviewers still cannot be reached then the opinion of the third reviewer will be used as the consensus rating
(4) Unplanned re-admission to the hospital within 48 h of hospital discharge	This outcome will be operationalized as re-admission before midnight of the second day full day after discharge. Thus, re-admission will occur before the 3rd midnight following hospital discharge
(5) Unplanned PICU readmission within 2 days of PICU discharge	This outcome will be operationalized as re-admission before midnight of the second full day after discharge. Thus, re-admission will occur before the 3rd midnight following PICU discharge
(6) PIM score predicted the risk of mortality	
(7) PICU mortality.	
(8) The PELOD score for PICU stay and the first 24 h in PICU	This score will be determined for both the entire PICU stay and the first 24 h in the PICU
(9) Ventilator-free days	Days alive and without invasive mechanical ventilation in the 28 days beginning at PICU admission will be recorded for the first PICU admission during each of the baseline and the post-randomization periods
Process of care	
(1) ‘Stat’ calls to physicians	Requests for immediate specific physician attendance to provide patient care to a patient admitted to an inpatient ward
(2) Code Blue calls	Immediate medical assistance of the resuscitation team and equipment

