**Table 4 Tab4:** **Clinical deterioration events**

		**Definition**	**SCDE***
1	Early transfer	<60 ml/kg intravenous or intraosseous fluid resuscitation given in the 12 h before transfer, no intravenous or intraosseous inotrope or vasoactive medications and no positive pressure ventilation (bag mask or endotracheal) in the 12 h before transfer	No
2	Noninvasive respiratory support	Positive pressure ventilation in the 12 h before transfer, but not intubated at the time of transfer. This category includes children receiving mask-delivered positive airway pressure at any stage in the 12 h before transfer and at the time of transfer. Mechanical ventilation during anesthesia for a scheduled procedure is not included	No
3	Invasive respiratory support	Intubated and/or receiving endotracheal ventilation at the time of transfer or intubated within 1 h of PICU admission	Yes
4	Circulatory	>60 ml/kg intravenous or intraosseous fluid resuscitation given in the 12 h before transfer, and administration of any intravenous or intraosseous inotrope or vasopressor at the time of transfer or at any stage in the 12 h preceding transfer. Patients in this category may also receive positive pressure ventilation (2)	Yes
5	Late transfer	Respiratory (3) *and* circulatory (4) support before transfer	Yes
6	Cardiopulmonary resuscitation	Chest compressions before transfer from ward area or within 1 h of PICU admission or ECMO instituted before or within 1 h of PICU admission	Yes
7	Death	Death on an inpatient ward, other than in those patients with DNR orders. Death may occur despite CPR (or intention to perform CPR if patient is pronounced dead without CPR). No transfer from ward area	Yes

*ECMO* extracorporeal membrane oxygenation therapy.

**SCDE* significant clinical deterioration event.

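### The nature-of-SCDE outcome compares a mean score among children who had an event, so it can shift when the mix of events changes, even if no serious event is prevented

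*Protocol article*

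**What the plan says.** Under Secondary analyses, the protocol article says: "A linear regression model, in which the within-hospital mean is the dependent variable, will be used to evaluate the nature of SCDE". The covariates are treatment arm, baseline mean and hospital size stratum.

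The scored population is described in two ways.
- Secondary outcomes: clinical lists "the nature of SCDE rated on the seven-point" Children's Resuscitation Intensity Scale.
- Table 3 says "Clinical deterioration events will be described by using the" same scale, and leaves out only urgent PICU admissions initiated in the operating room.

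Table 4 gives the scale. Category 1, early transfer, begins with "<60 ml/kg intravenous or intraosseous fluid resuscitation given in the 12 h before transfer". Categories 1 and 2 are marked as not SCDE, and categories 3 to 7 as SCDE.

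The intervention's care recommendations (Intervention: BedsidePEWS) cover "vital sign assessment, secondary review, continuous monitoring and ICU consultation".

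The main secondary outcome is analysed on a different base: "Significant clinical deterioration events, Code Blue events, stat calls and urgent PICU consultations per 1000 patient-days will be evaluated using Poisson regression".

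**The concern.** No category in Table 4 fits a child who has no event, so the within-hospital mean can only be taken over children who had one. Becoming an event happens after randomization, and the intervention aims at earlier identification and referral. A difference between arms in this mean may therefore reflect a change in which children are scored and not a change in how far deterioration had gone. The baseline mean and the stratum do not adjust for a change in the number or mix of events after the intervention starts.

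The two descriptions of the scored population matter because each leaves the mean open to a different shift. With categories 1 to 7, added early transfers dilute it. With categories 3 to 7, early transfers do not enter, but preventing the milder SCDE leaves a more severe remainder. What is at stake is the interpretation of one secondary outcome, listed directly after SCDE in Table 3.

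**Working it through.** The article gives no effect size, standard deviation or power for this outcome, so there is no stated figure to reproduce. The check is the arithmetic of a mean taken over events.

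**Inputs from the document (Sample size and assumptions)**
- "there are 1052 urgent ICU admissions/year, of which we estimate 40% involve SCDE, for a rate of 2 per thousand patient days".
- The detectable SCDE reduction is 31%.

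**Inputs assumed here**
- Mean score 4 among SCDE (range 3.5 to 4.5).
- Mean score 1.2 among other events (range 1.0 to 1.5).
- For the SCDE-only case, 40 events split 24/6/4/4/2 over categories 3 to 7.

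**All clinical deterioration events scored (categories 1 to 7)**

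Per 100 events, the baseline mean is (60 × 1.2 + 40 × 4)/100 = 2.32.

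Adding a fraction x of score-1 transfers changes a mean M to (M + x)/(1 + x), a change of −x(M − 1)/(1 + x). This is negative whenever M is above 1, so the direction needs no assumption.

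| Scenario | Calculation | Mean | Change |
|---|---|---|---|
| 10 extra early transfers, no SCDE prevented | 242/110 | 2.20 | −5% |
| 20 extra, no SCDE prevented | 252/120 | 2.10 | −9.5% |
| 30 extra, no SCDE prevented | 262/130 | 2.02 | −13% |
| 31% of SCDE prevented, no extra transfers | (72 + 27.6 × 4)/87.6 | 2.08 | −10% |

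Over the assumed ranges the baseline mean is 2.00 to 2.70. Adding 20% early transfers lowers it by 0.17 to 0.28. Preventing 31% of SCDE lowers it by 0.17 to 0.30. The mean barely separates the two.

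**Only SCDE scored (categories 3 to 7)**

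Baseline: (24 × 3 + 6 × 4 + 4 × 5 + 4 × 6 + 2 × 7)/40 = 154/40 = 3.85. Extra score-1 transfers have no effect.
- Prevent 31% (12.4 events), all in category 3: (154 − 37.2)/27.6 = 4.23, a rise of 10%.
- Prevent the 6 events in categories 6 and 7 instead: (154 − 38)/34 = 3.41, a fall.

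The direction depends on whether the prevented events score below or above the mean.

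**Same dilution on a patient-day base**

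An SCDE rate of 2 per 1000 patient-days at a 40% share implies 2/0.4 = 5 urgent admissions per 1000. With 20% more, all early transfers, the total is 6 per 1000. The SCDE rate stays at 2 (rate ratio 1.00), and only the category 1 rate rises, by 1 per 1000.

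**The case against.** The strongest reply is that the plan already holds the safeguard. The SCDE rate per 1000 patient-days is the main secondary outcome. It would show no effect under pure dilution and would fall if category 3 events were prevented. How often events occur and how advanced they are when they occur are separate questions, and the plan lists both. No power statement or decision rule rests on the mean. All of this stands and limits the importance of the point. It does not repair the mean itself, for which the analysis section fixes a between-arm regression.

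A shift towards early transfer can also be the intended benefit. If would-be SCDE become early transfers, the all-events mean falls, and rightly so. The mean cannot tell that apart from added transfers of children who would never have had an SCDE.

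Two stronger readings are tempting, and the document supports neither.
- A reader might infer that the two scored populations always bias the result in opposite directions. They do so only in chosen scenarios: the last SCDE-only example above moves the mean down, the correct direction.
- A reader might infer that the intervention will add transfers. The recommendations concern ICU consultation, which could avert transfers as well as prompt them. The stated hypothesis is no increase in resource use, and Table 1 cites a pilot evaluation without additional resources. That hypothesis is under test and so gives no protection, but nothing in the document supports any particular number of extra transfers.

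**Conclusion.** The point holds as a minor one. The nature of SCDE is compared between arms as a mean conditional on an event after randomization that the intervention can affect, and the document names two different scored populations. Under the Table 3 population, added score-1 transfers lower the mean with no SCDE prevented. Under the SCDE-only population, preventing SCDE with below-average scores raises it.

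These directions follow from arithmetic alone. The sizes, about 5% to 13% down in the first case and about 10% up in the second, depend on assumed score means, category splits and numbers of extra transfers. Only the 40% share and the 31% reduction come from the document.

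The primary outcome and the SCDE rate are not affected. A reader might take this as grounds to doubt the trial's main findings on clinical deterioration. It is not, because those findings rest on the SCDE rate, which uses patient-days as its base.

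**What to change.** 1. Name one scored population throughout: the clinical deterioration events of Table 3, categories 1 to 7. Bring Secondary outcomes: clinical and Secondary analyses into line with it.
2. Make the between-arm comparison on hospital-level rates per 1000 patient-days at a small number of cut-points stated in advance, for example all events and category 6 or above. Use the count model, baseline term and stratum already planned for SCDE. A cut at category 3 or above is not needed, since it is the planned SCDE rate.
3. Report the score distribution and mean among events descriptively only, beside those rates.

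The cost is wording. The categories come from the scale already in use, and patient-days are already needed for the SCDE rate. The downside is a few correlated secondary rates in place of one mean, with sparse counts at the top of the scale. The Discussion expects about 200 cardiac arrests in 22 hospitals, or 200/22 ≈ 9 per hospital.
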